7.3.5 Gastrointestinal

Gastrointestinal side effects from pentoxifylline appear to be dose-related. The development of nausea, vomiting, bloating, dyspepsia, or other gastrointestinal symptoms of any toxicity grade that is likely due to PTX will result in dosage reduction of PTX to 400mg po bid (one tablet twice daily instead of one tablet thrice daily). If this does not result in a reduction of symptoms of at least one toxicity grade, then PTX will be permanently discontinued.

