As a safety measure, a peripheral IV heplock will then be placed at the IU ICRC to reduce the number of venous punctures required for the serial blood draws required to estimate insulin resistance. The heplock will also facilitate the infusion of IV fluids if NTG-induced hypotension occurs during the brachial artery reactivity testing. By performing just one venous puncture for placement of the IV heplock, the risks of bleeding, bruising, pain, and infection to the subject will be minimized; this will also reduce the risk of accidental occupational exposure of potentially infectious material to the study team. The heplock will then be removed after assurance of subject hemodynamic stability once brachial reactivity testing is completed.

Safety and adverse events will be assessed at each study visit. Study participants will be encourage to notify the study team in between these visits if symptoms occur that may be related to study drug. In the event of an adverse event possibly related to study drug, a full assessment (examination, laboratories) will be performed immediately. Study discontinuation will occur if a Grade 3 or 4 event (per Division of AIDS Toxicity Grading System <http://roc.s-3.com/members/download/adulttox.pdf>), serious adverse event, or hospitalization likely due to study drug occurs. For less severe events thought to be related to study drug, then PTX or placebo dosing will be reduced by one pill (e.g. 400mg of active agent) and symptoms, signs, and laboratories will be reassessed after one week. If the adverse event continues at the same severity or improves only modestly, then dosing will be reduced by one more pill and again the participant will be reassessed after one week. If the adverse event persists at this time, then the subject will be discontinued from the study. However, if symptoms resolve after dose reduction, then the subject will continue on study using the new dosage level. The subject, of course, will have the option of withdrawing from the study at any time. All subjects who stop study drug prematurely due to an adverse event will be followed weekly until resolution. Please see Human Subjects Protection for further details on safety monitoring.

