1. ADVERSE EVENT MANAGEMENT

The management guidelines listed here are for the adverse events most likely to occur during this protocol. Grade III or IV abnormalities (defined using the Division of AIDS Table for Grading Adult Adverse Experiences) will prompt immediate discontinuation of the drug. For all toxicities that requires pentoxifylline to be permanently discontinued, relevant clinical and laboratory tests will be repeated as needed until there is final resolution or stabilization of the toxicity. Clinical management decisions will be made by the principal investigator in conjunction with the subject’s primary caregiver; care plans and outcomes must be included in the source documentation. Serious adverse events (SAEs) will be documented on CRFs and forwarded to the Indiana University IRB within 10 working days of the event.

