7.3.6 Neurologic

Neurologic side effects from pentoxifylline appear to be dose-related. The development of dizziness, agitation/nervousness, blurred vision, or other neurologic symptoms of any toxicity grade that is likely due to PTX will result in dosage reduction of PTX to 400mg po bid (one tablet twice daily instead of one tablet thrice daily). If this does not result in a reduction of symptoms by at least one toxicity grade, then PTX will be permanently discontinued.

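### The GI and neurologic dosing rules (7.3.5, 7.3.6) conflict with 3.3 after a failed first reduction, and their any-grade wording conflicts with the Grade 3-4 stop in 3.3 and 7.2

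*Combined protocol and SAP*

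**What the plan says.** Study drug is one 400 mg tablet three times daily (5.1).

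**Section 3.3** covers events less severe than Grade 3-4 that are thought to be drug-related: "then PTX or placebo dosing will be reduced by one pill", with reassessment after a week. It continues: "If the adverse event continues at the same severity or improves only modestly, then dosing will be reduced by one more pill", again with reassessment after a week. The last step is: "If the adverse event persists at this time, then the subject will be discontinued from the study". For severe events likely due to study drug the rule is: "Study discontinuation will occur if a Grade 3 or 4 event". No exception is made for gastrointestinal or neurologic events.

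**Section 7.3.5** (gastrointestinal) says that "other gastrointestinal symptoms of any toxicity grade that is likely due to PTX will result in dosage reduction of PTX to 400mg po bid". It then says: "If this does not result in a reduction of symptoms of at least one toxicity grade, then PTX will be permanently discontinued". **Section 7.3.6** has the same two steps, the first worded as "other neurologic symptoms of any toxicity grade that is likely due to PTX will result in dosage reduction of PTX to 400mg po bid". Neither says when the response is to be judged.

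**Section 7.2** stops PTX permanently for Grade 3 or 4 events, unless there is compelling evidence that PTX is not the cause. The opening of section 7 and section 10.3.2.3 both say that Grade III or IV abnormalities "will prompt immediate discontinuation of the drug".

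**Section 2.4.8**, adapted from the package insert, advises one step down to two tablets a day for digestive and central nervous system effects, then discontinuation if they persist.

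**The concern.** These are mandatory dosing instructions for the side effects that the protocol itself expects. In the pilot at this dose (2.3.3), most subjects noticed looser stools, although none was treatment-limiting. Staff who open 3.3 and staff who open 7.3.5 would handle the same subject differently once the first reduction has failed. Read literally, 7.3.5 and 7.3.6 also continue dosing in a subject whose drug-related event has reached Grade 3 or 4. What is at stake is consistent and safe handling of blinded study drug across the 26 subjects.

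**Working it through.** The plan gives no figure to reproduce and no statistical calculation applies. The check sets the rules side by side and converts each to tablets per day.

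Dose levels: 3 × 400 = 1200 mg/day at the start; 2 × 400 = 800 mg/day after one reduction; 1 × 400 = 400 mg/day after two.

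| Event judged drug-related | Section 3.3 | Sections 7.3.5 / 7.3.6 | Section 7.2 |
|---|---|---|---|
| Grade 1-2, at onset | 2 tablets | 2 tablets | not applicable |
| Grade 2, unchanged on 2 tablets | 1 tablet, reassess in one week | 0, permanently | not applicable |
| Grade 2 falling to Grade 1 on 2 tablets | 1 tablet if the improvement is judged only modest | stays at 2 tablets | not applicable |
| Grade 1, eased but still Grade 1 | 1 tablet if the improvement is judged only modest | 0, permanently | not applicable |
| Grade 3-4 | 0 (study discontinuation) | 2 tablets | 0, permanently |

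**Conflict (a), Grade 1-2.** The rules agree on the first step. After an unchanged response, 3.3 orders 400 mg/day and 7.3.5/7.3.6 order none, so both cannot be followed. Rows three and four show that the tests for failure can also pull in opposite directions. Under the one-grade test a fall from Grade 2 to Grade 1 is a success, while a Grade 1 event succeeds only if it resolves (1 − 1 = 0). Under 3.3 either may count as modest improvement and lead to one tablet. Section 3.3 fixes a one-week interval; 7.3.5 and 7.3.6 fix none.

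**Conflict (b), Grade 3-4.** The trigger in 7.3.5 and 7.3.6 is an event likely due to PTX, at any grade. The only exception in 7.2 is for events shown not to be due to PTX, which is the opposite attribution. The exception therefore cannot reconcile the two.

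**Does another text settle it?** No clause says which rule takes precedence. Section 7.1 names event types as exceptions dealt with later; 7.2 makes no such exception for gastrointestinal or neurologic events. The liver-test rule (7.3.2) and the rash rule (7.3.4) each restate the Grade 3-4 stop, but 7.3.5 and 7.3.6 do not. That pattern points to an omission, not a deliberate exemption. Section 5.1 only permits reductions in 400 mg decrements and conflicts with neither rule.

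**The case against.** The best defence is that section 8 sends staff to section 7 as a whole. That section opens with the Grade III/IV stop and repeats it in 7.2 before 7.3.5 is reached. Section 3.3 reserves stepwise reduction for less severe events. The section 7 opening gives clinical management decisions to the principal investigator together with the primary caregiver. All procedures take place at one research center. The pilot saw no treatment-limiting gastrointestinal event.

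Most of this stands, and it lowers the practical risk. It also weakens reliance on the section 7 opening and 10.3.2.3 as separate evidence. They share one sentence about abnormalities, and in 10.3.2.3 it follows a list of safety laboratory tests, so its reach to symptoms is arguable. The clear conflicting texts are 3.3 and 7.2. The defence does not make the instructions compatible. The section 8 reference favours section 7 over 3.3 but cannot resolve a conflict inside section 7, and 3.3 itself refers readers to the human-subjects section for further safety detail.

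A reader might infer more from three features, and the documents do not support it:

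- **Leaving the study versus stopping drug.** Section 3.3 speaks of the first and 7.3.5/7.3.6 of the second, but section 8 lists drug-related toxicity as a reason for study discontinuation, which largely merges the two.
- **Lost week-8 FMD.** An early stop could leave the primary endpoint unmeasured, but that could happen under either rule alone. The early-evaluation rule in 6.2.3 is written for subjects who give notice of termination and does not mention protocol-mandated stops. Obtaining week-8 FMD after a toxicity stop is a separate question about follow-up under intention to treat.
- **A further conflict with 7.1.** That section lets Grade 1-2 events continue on protocol, and a protocol-specified dose reduction is a way of continuing.

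**Conclusion.** The point holds as a minor internal inconsistency. After a failed first reduction the instructions differ by one tablet a day (400 mg/day against none), with different tests of failure and a reassessment interval in only one rule. For drug-related Grade 3-4 gastrointestinal or neurologic events they differ by two tablets a day (800 mg/day against none).

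The conclusion rests on the current wording and on the absence of a precedence clause. It does not assume that anyone intended to keep such subjects on drug; the any-grade phrase is more likely a slip. The documents give no rate of graded drug-related events, so the number of subjects affected cannot be estimated. No effect on the endpoint, the power or the intention-to-treat result is shown.

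**What to change.** 1. In 7.3.5 and 7.3.6, replace the any-grade qualifier with *of Grade 1 or 2*, which leaves Grade 3-4 events under 7.2.
2. In 3.3, state that gastrointestinal and neurologic events follow 7.3.5 and 7.3.6: one step to two tablets a day, reassessment at one week by the one-grade test, then stop study drug if the test is not met. This is consistent with the advice in 2.4.8.
3. Write the one-week reassessment interval into 7.3.5 and 7.3.6.

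The cost is wording edits in three sections. Dose modifications are already recorded on the case report forms (6.3.5), so no new data item is needed. The sample size and the analysis are unchanged.

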7.3.6 Neurologic

Neurologic side effects from pentoxifylline appear to be dose-related. The development of dizziness, agitation/nervousness, blurred vision, or other neurologic symptoms of any toxicity grade that is likely due to PTX will result in dosage reduction of PTX to 400mg po bid (one tablet twice daily instead of one tablet thrice daily). If this does not result in a reduction of symptoms by at least one toxicity grade, then PTX will be permanently discontinued.

7.4 Nitroglycerin

7.4.1 Hypotension

The primary risk inherent with the administration of nitroglycerin as part of the brachial reactivity measurements is transient hypotension. Subjects will be questioned regarding the use of sildenafil, vardenafil, or tadalafil; if the subject used any of these agents within 72 hours before the ultrasound or intends to use any of these agents within 72 hours after the ultrasound, the visit will be rescheduled. To protect against the risks of nitroglycerin administration, trained medical personnel will monitor the subject’s blood pressure throughout brachial reactivity testing. If the subject becomes symptomatic (e.g. dizzy, perspiring, weak, or nauseated) or if the systolic blood pressure falls below 80mmHg, the study will be stopped immediately. The subject will be placed the Trendelenberg position, and if necessary, administered 0.9% NS (normal saline) through the previously placed IV heplock until the subject is stable.

Subjects who have an “excessive drop” in systolic blood pressure or have any other serious adverse event after receiving nitroglycerin will not undergo NTGMD as part of the brachial reactivity testing; however, FMD evaluations will still be performed. An “excessive drop” is defined as a decrease in systolic blood pressure to less than 80 mmHg, or a 30 mmHg or greater decrease from the pre-nitroglycerin systolic blood pressure.

- - 1. Headache

If the patient develops a headache that lasts for over an hour after the receipt of nitroglycerin, an analgesic will be recommended.

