After this baseline evaluation, the measurement of endothelium-dependent vasodilation, or FMD, due to increased blood flow will begin. The forearm pressure cuff will be inflated to 250 mmHg for 5 minutes. At that time, imaging will be switched to B-mode. At 60 and 90 seconds after cuff deflation, three consecutive cardiac cycles of B-mode images of the brachial artery to the disc will be acquired and stored. The greater of the two diameters measured at these time points will be used for FMD analysis.

After 15 minutes from time of cuff deflation, the measurement of endothelium-independent vasodilation, or NTGMD, will begin. As before, three consecutive cardiac cycles of B-mode images of the brachial artery stored to the disc. Blood pressure measurement will then be repeated as a new baseline. Nitroglycerin (400 mcg SL) will then be administered. Three minutes later, three consecutive cardiac cycles of B-mode of the brachial artery stored to the disc and backed-up to a magneto-optical disk and the IU server with password protection.

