10.3.2.4 Nitroglycerin. Brachial artery reactivity testing will be performed in a controlled setting in the Indiana Clinical Research Center. To protect against the risks of nitroglycerin administration, registered nurses in the ICRC will monitor the subject’s blood pressure throughout brachial reactivity testing. Subjects with inherent resting hypotension will be excluded from the NTG-mediated flow dilation portion of the brachial reactivity testing. If the subject becomes symptomatic (e.g. dizzy, perspiring, weak or nauseated, or if the systolic blood pressure falls below 80mmHg or more then 30mmHg below their baseline systolic blood pressure, the study will be stopped immediately). The patient will be placed in Trendelenberg position and be given fluids through the previously placed IV heplock if the blood pressure does not recover spontaneously. If the patient develops a headache, an analgesic will be recommended.

10.3.2.5 Withholding Antiretroviral Therapies. Subjects will be included if their HIV caregiver has decided that antiretroviral therapy is not required and thus has been free of cART for at least six months time. There is a minimal risk to the subjects by continuing to refrain from use of antiretrovirals during the short course of this trial (maximum 11 weeks from screening to last main visit). To reduce this small risk, subjects must have CD4 cell counts above 350/µL, which is the level that the Department of Health and Human Services HIV Management Guidelines (<http://aidsinfo.nih.gov/contentfiles/AdultandAdolescentGL.pdf>) states that initiation of ART is not required. Per these guidelines, CD4 cell counts need only be routinely monitored every 3-4 months (12-16 weeks) in the untreated, asymptomatic patient. Therefore, the study course for each subject should be completed by the time their CD4 cell count would normally be rechecked in the clinic. However, if the subject develops signs, symptoms, or conditions associated with a reduction in CD4 cell count, the subject will have their CD4 cell count checked immediately. The principal investigator and the primary caregiver will then decide if antiretroviral therapies should be started immediately with permanent discontinuation of this study.

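### Sections 7.4.1 and 10.3.2.4 give different immediate-stop triggers for nitroglycerin testing when systolic pressure falls by more than 30 mmHg without symptoms but stays at 80 mmHg or above

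*Combined protocol and SAP*

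**What the plan says.** Section 7.4.1 identifies transient hypotension as the main risk of the nitroglycerin dose. It stops testing if the participant has symptoms, or "if the systolic blood pressure falls below 80mmHg, the study will be stopped immediately". Management follows: "The subject will be placed the Trendelenberg position", with saline if needed.

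A second paragraph of 7.4.1 defines an excessive drop as a systolic pressure below 80 mmHg or "a 30 mmHg or greater decrease from the pre-nitroglycerin systolic blood pressure". A participant with an excessive drop, or with another serious adverse event after the dose, "will not undergo NTGMD as part of the brachial reactivity testing; however, FMD evaluations will still be performed". No stop or management step is attached to the 30 mmHg limit.

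Section 10.3.2.4 stops for symptoms or "if the systolic blood pressure falls below 80mmHg or more then 30mmHg below their baseline systolic blood pressure". It then says "The patient will be placed in Trendelenberg position and be given fluids through the previously placed IV heplock", and that sentence ends with the condition that the pressure has not recovered spontaneously.

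Section 3.4 sets the order of events. FMD is imaged at 60 and 90 seconds after cuff release, and the nitroglycerin step starts 15 minutes after release. Just before the dose, "Blood pressure measurement will then be repeated as a new baseline". After the dose one imaging step remains: "Three minutes later, three consecutive cardiac cycles of B-mode of the brachial artery stored to the disc".

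**The concern.** Both sections are current, operative text for one procedure, and the human-subjects section is stricter than the adverse-event section. A nurse working from 7.4.1 who sees an asymptomatic fall from 120 to 85 mmHg finds no instruction to stop. A nurse working from 10.3.2.4 must stop at once.

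The excessive-drop paragraph does not close the gap. It uses a different limit (30 or more, against more than 30), names its reference reading differently, and governs whether NTGMD is done rather than whether the session ends. It also does not say whether it applies to the current visit or to later ones. Its statement that FMD is still performed points to later visits, because FMD at the current visit is already complete when nitroglycerin is given.

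What is at stake is consistent handling of a known procedural risk. No estimate or test in the analysis plan is involved.

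**Working it through.** The plan states no figure to reproduce. The check sets the rules side by side and finds where they differ.

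**Inputs.** S is the systolic pressure just before the dose and P the value after it, in whole mmHg, with no symptoms. Baseline in 10.3.2.4 is taken as S, following section 3.4.

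- 7.4.1 stop: P < 80.
- 7.4.1 NTGMD bar: P < 80 or S − P ≥ 30.
- 10.3.2.4 stop: P < 80 or S − P > 30.

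**Where the stop rules differ.** 10.3.2.4 stops and 7.4.1 does not when 80 ≤ P and S − P > 30, that is, when 80 ≤ P ≤ S − 31. This needs S ≥ 111.

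| Pre-dose S | S − 31 | Post-dose values where only 10.3.2.4 stops |
| --- | --- | --- |
| 110 | 79 | none |
| 111 | 80 | 80 |
| 120 | 89 | 80 to 89 |
| 140 | 109 | 80 to 109 |
| 160 | 129 | 80 to 129 |

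At S = 110 or below, any fall of more than 30 mmHg takes P below 80, so both rules stop. For 120 to 85, the fall is 35: 7.4.1 does not stop because 85 ≥ 80, and 10.3.2.4 stops because 35 > 30.

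**Falls of exactly 30.** When P = S − 30 and P ≥ 80, for example 120 to 90, 7.4.1 counts an excessive drop and bars NTGMD, but neither section stops the test.

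**Is the range realistic under the plan?** A main visit is rescheduled if systolic is below 90 mmHg (sections 3.4 and 6.3.8.13), and exclusion for high pressure begins above 160 mmHg at screening (section 4.2). Pre-dose values from 111 to 160 are therefore compatible with eligibility.

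**How many participants?** Testing is scheduled at weeks 0, 4 and 8, so 26 × 3 = 78 doses are planned if all 26 participants complete and none is barred. The documents give no rate of hypotension after nitroglycerin. The width of the bands in the table says where the rules differ, not how often.

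**Effect on endpoints.** FMD at the visit is acquired before the dose. Section 9.3.2 has the change in FMD as primary outcome, and NTGMD is not among the secondary endpoints in section 9.3.3.

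**The case against.** The best defence is that the sections differ without contradicting each other. The triggers in 10.3.2.4 are those in 7.4.1 plus one, 7.4.1 never tells staff to continue after a large fall, and stopping on any listed trigger satisfies both. Section 7.4.1 also already treats a 30 mmHg fall as excessive. If its bar covers the current visit, the one remaining image is not taken anyway. There is one dose per visit, intravenous access is in place, and both sections require pressure monitoring throughout. All of this stands, and it limits the harm. It does not supply a stop in 7.4.1, which is the section staff would consult for managing the event.

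Three stronger readings are tempting, and the documents do not support them.

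- A reader might infer that 10.3.2.4 requires Trendelenburg positioning after every fall of more than 30 mmHg. The condition about spontaneous recovery can be read to govern positioning as well as fluids, so only the stop is clearly required.
- A reader might infer that baseline in 10.3.2.4 is the seated reading described in 6.3.8.3, which would move the limit. That section never calls its reading a baseline, whereas section 3.4 gives that name to the pre-dose reading. The ambiguity is weak.
- A reader might infer that the discrepancy threatens the FMD result. The order of testing rules that out for the visit concerned, and 7.4.1 keeps FMD in place after an excessive drop.

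**Conclusion.** The inconsistency is real and minor. For an asymptomatic participant with a pre-dose systolic above 110 mmHg, 10.3.2.4 requires an immediate stop and 7.4.1 does not when the post-dose value is at least 80 mmHg and more than 30 mmHg lower. Below that range of pre-dose values the stop rules agree. Both statements assume that baseline means the pre-dose reading.

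The number of participants affected cannot be estimated from the documents. Sample size, type I error and the primary analysis are untouched. The most that changes in the data is whether a few NTGMD images are taken. The text should be corrected because the two sections should give the same instruction for a recognised procedural risk, and the correction costs little.

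**What to change.** Use one stop trigger, worded identically in 7.4.1 and 10.3.2.4: stop nitroglycerin testing immediately for symptoms, a systolic pressure below 80 mmHg, or a fall of 30 mmHg or more from the pre-nitroglycerin reading, identified as the new baseline in section 3.4. This adopts the limit that already defines an excessive drop, so one threshold and one reference reading serve both purposes.

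Leave the rest as it is:

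- Keep Trendelenburg positioning and fluids for symptoms, pressure below 80 mmHg, or pressure that does not recover spontaneously. An asymptomatic change from 160 to 130 that recovers unaided would stop the test without requiring further management.
- Keep the present NTGMD bar for an excessive drop or another serious adverse event after nitroglycerin. Do not extend it to symptoms alone. If brief nausea at week 0 led to NTGMD being omitted at that visit and later ones, the internal control described in section 2.2.1 would be lost for that participant at all three visits.

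The cost is a text amendment to two sections, with no added visits, staff or equipment. Falls of exactly 30 mmHg that stay at or above 80 mmHg become stops, which they are in neither section now. A few NTGMD images may be lost. If the existing bar covers only later visits, the current-visit image is lost when the stop precedes it. If the bar already covers the current visit, the change loses none for falls of 30 mmHg or more.

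### Sections 7.4.1 and 10.3.2.4 state different immediate-stop rules after nitroglycerin; for a symptom-free subject they part above a reference systolic of 110 mmHg

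*Combined protocol and SAP*

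**What the plan says.** Three places in the combined protocol and SAP bear on this.

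- **Section 7.4.1, first paragraph (stop rule).** There are two triggers. One is symptoms: "If the subject becomes symptomatic (e.g. dizzy, perspiring, weak, or nauseated". The other is an absolute limit: "if the systolic blood pressure falls below 80mmHg, the study will be stopped immediately".
- **Section 7.4.1, second paragraph (excessive drop).** This is defined as a systolic value under 80 mmHg "or a 30 mmHg or greater decrease from the pre-nitroglycerin systolic blood pressure". A subject who has one after nitroglycerin "will not undergo NTGMD as part of the brachial reactivity testing; however, FMD evaluations will still be performed".
- **Section 10.3.2.4 (stop rule again).** The symptom trigger is the same, but the pressure trigger has two limbs: "if the systolic blood pressure falls below 80mmHg or more then 30mmHg below their baseline systolic blood pressure, the study will be stopped immediately".

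Section 3.4 fixes the order of events. FMD images come first. Then: "After 15 minutes from time of cuff deflation, the measurement of endothelium-independent vasodilation, or NTGMD, will begin". Images are stored and, just before the dose, "Blood pressure measurement will then be repeated as a new baseline". Nitroglycerin follows, and the NTGMD images are taken three minutes later.

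**The concern.** Sections 7.4.1 and 10.3.2.4 describe the same event and use the same consequence, an immediate stop, but their limits are not the same. Section 7.4.1 sits in the adverse event chapter that staff would work from. Section 10.3.2.4 sits in the human-subjects chapter, which describes the protection offered. As written, the protection described in the second is wider than the stop sentence in the first.

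Two things are at stake. The first is safety conduct: Section 7.4.1 itself names transient hypotension as the main risk of the nitroglycerin step, which the schedule places at all three main visits. The second is data. A stop before the three-minute images means no NTGMD value for that visit, and Section 2.2.1 presents NTGMD as the internal control that helps to separate endothelial from smooth-muscle dysfunction.

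**Working it through.** The plan states no figure to reproduce. The check compares the two stop sentences for a subject without symptoms, since the symptom trigger is common to both.

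**Inputs.** Let R be the reference systolic and S the systolic after nitroglycerin, in whole mmHg.
- Section 7.4.1 stop: S < 80.
- Section 10.3.2.4 stop: S < 80, or R − S > 30.
- Section 7.4.1 excessive drop: S < 80, or R − S ≥ 30.
- Range of R considered: 90 (the Section 4.2 floor for testing at a main visit) to 160 (the Section 4.2 ceiling at screening).

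**Step 1: where the stop sentences agree.** A fall of more than 30 means S < R − 30. If R ≤ 110, then R − 30 ≤ 80, so any such fall already gives S < 80. The second limb adds nothing and the rules coincide.

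**Step 2: where they differ.** If R > 110, they differ for 80 ≤ S < R − 30, a band R − 110 mmHg wide.

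| R | S at which only 10.3.2.4 orders a stop | Width R − 110 (mmHg) |
| --- | --- | --- |
| 90, 100, 110 | none | 0 |
| 120 | 80–89 | 10 |
| 130 | 80–99 | 20 |
| 140 | 80–109 | 30 |
| 160 | 80–129 | 50 |

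Example: R = 140, S = 100. The fall is 140 − 100 = 40, which exceeds 30, and 100 is not below 80. Section 10.3.2.4 orders a stop; the stop sentence of 7.4.1 does not.

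**Step 3: does the excessive-drop paragraph close the gap?** That depends on which test it governs, which the text does not say.
- *Later tests only.* FMD is finished before nitroglycerin is given, so the statement that FMD will still be performed makes most sense for a later visit. This is the more natural reading, and it leaves the whole band in Step 2 open.
- *The current test as well.* The two sections then nearly agree. What remains is the boundary, ≥ 30 against > 30. At R = 130 and S = 100 the fall is exactly 30: an excessive drop in 7.4.1, but not a trigger in 10.3.2.4. For each R of 110 or more, exactly one whole-mmHg value, S = R − 30, is treated differently.

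**Step 4: the reference reading.** Section 7.4.1 measures the excessive drop from the pre-nitroglycerin value, whereas 10.3.2.4 refers to the subject's baseline. Section 3.4 calls the reading just before nitroglycerin a new baseline, so the two terms most naturally mean the same reading. But Section 6.3.8.3 also requires three seated readings before the ultrasound, and 10.3.2.4 does not name which reading it means.

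**The case against.** The strongest reply is that 7.4.1 never tells staff to carry on after a 30 mmHg fall. It contains the same two numbers, 80 and 30, and its second paragraph withholds NTGMD after such a fall. On one reading, a subject who goes from 140 to 100 mmHg loses NTGMD under both sections. On the other, 7.4.1 is silent, and staff who stop under 10.3.2.4 breach nothing in it. This stands: a reader might infer that the sections give opposite instructions, and they do not. What remains is that one section mandates a stop and the other does not, and that the scope of the excessive-drop paragraph is left open.

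It can also be said that the inequality mismatch is a contradiction only if the excessive drop and the stop criterion are meant as one rule, and that the baseline wording is largely settled by Section 3.4. Both are fair. These are secondary wording points, to be tidied in the same edit.

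The consequences for the data are limited. FMD images are already stored when nitroglycerin is given, and NTGMD is not among the objectives in Section 1 or the endpoints analysed in Sections 9.3.2 and 9.3.3.

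Two stronger inferences are tempting and are not supported:
- **A count of affected scans.** This would need the distribution of resting systolic pressure and of the fall after nitroglycerin. The documents give neither.
- **Differential loss of NTGMD by arm.** The Drug Interactions text in Section 2.4 mentions small pressure decreases in some patients on pentoxifylline. The General Precautions text in the same section says that controlled trials do not show hypotension more often than with placebo. Patients on antihypertensive drugs, for whom the pressure monitoring is advised, are excluded at screening. An arm difference is speculation.

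**Conclusion.** The point holds as an internal inconsistency in a safety rule. For a symptom-free subject, the two immediate-stop sentences agree at a reference systolic of 110 mmHg or below. Above that they disagree over a band R − 110 mmHg wide, reaching 50 mmHg at the screening ceiling of 160. This follows from the stated limits alone and needs no outside assumption. If the excessive-drop paragraph is meant to end the current test, the disagreement shrinks to a fall of exactly 30 mmHg and the naming of the reference reading; the text does not settle which is meant.

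The effect is confined to how staff respond to a pressure reading and to whether an NTGMD value exists for that visit. The primary FMD analysis and the sample size are unaffected. The case for acting rests on this being a safety threshold that is almost free to clarify, not on any expected loss of data.

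**What to change.** Reconcile Sections 7.4.1 and 10.3.2.4 so that both carry a single stop rule with one set of limits, one inequality and one named reference reading. If the reading meant is the one that Section 3.4 takes just before the dose, say so in both places. State whether an excessive drop ends the current test, bars later NTGMD tests, or both. Which limits to adopt is a clinical decision for the investigators, and no view is given here.

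The cost is a wording change in two sections. A CRF entry for which limit was met and whether the three-minute images were obtained would help to explain missing NTGMD values. It is optional, since no planned endpoint analysis uses NTGMD.
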